## Abstract

**Background:**

Hip fractures in older people are associated with high morbidity, mortality, disability and reduction in quality of life. Traditionally people with hip fracture are cared for in orthopaedic departments without additional geriatric assessment. However, studies of postoperative rehabilitation indicate improved efficiency of multidisciplinary geriatric rehabilitation as compared to traditional care. This randomized controlled trial (RCT) aims to investigate whether an additional comprehensive geriatric assessment of hip fracture patients in a special orthogeriatric unit during the acute in-hospital phase may improve outcomes as compared to treatment as usual in an orthopaedic unit.

**Methods/design:**

The intervention of interest, a comprehensive geriatric assessment is compared with traditional care in an orthopaedic ward. The study includes 401 home-dwelling older persons >70 years of age, previously able to walk 10 meters and now treated for hip fracture at St. Olav Hospital, Trondheim, Norway. The participants are enrolled and randomised during the stay in the Emergency Department. Primary outcome measure is mobility measured by the Short Physical Performance Battery (SPPB) at 4 months after surgery. Secondary outcomes measured at 1, 4 and 12 months postoperatively are place of residence, activities of daily living, balance and gait, falls and fear of falling, quality of life and depressive symptoms, as well as use of health care resources and survival.

**Discussion:**

We believe that the design of the study, the randomisation procedure and outcome measurements will be of sufficient strength and quality to evaluate the impact of comprehensive geriatric assessment on mobility and other relevant outcomes in hip fracture patients.

**Trials registration:**

ClinicalTrials.gov, NCT00667914

## Background

Every year about 9000 persons undergo hip fracture surgery in Norway [1]. Hip fractures among older people are associated with high morbidity, mortality, disability and subsequent hospital and societal costs as well as reduction in quality of life [2-6]. A Study from Oslo, Norway showed that the proportion of patients living in nursing homes increased from 15% before to 30% after the hip fracture; the proportion walking without any aid decreased from 76 to 36%; and 43% of the patients lost their pre-fracture ability to mobilise outside their own home [7].

Older people with hip fracture often have extensive co-morbidity which is associated with functional impairments and frailty. The frailty phenotype is defined by deterioration of multiple organ systems including the neurological, musculoskeletal, cardiovascular, metabolic or immunological systems [8]. Frailty has been shown to be associated with falls resulting in injuries [9].

Previous studies show improved outcomes when older people with hip fracture are cared for by a specialist multidisciplinary team [10-12]. Reports indicate improved efficiency of multidisciplinary geriatric rehabilitation especially regarding delirium, recurrent falls and fractures, and use of institutional care [13-15]. There is now a growing body of evidence supporting this approach [16,17] and recently evidence-based guidelines as for treating hip fracture patients have been developed,[18] although context and organisation of so-called hip-units differs widely [19].

However, the findings in these studies are not conclusive and we still do not know which specific input, if any, is crucial to beneficial effects. Is it the management of medical complications; is it a goal-oriented intervention by one single professional staff-member, i.e. the physiotherapist, nurse or physician; or is it related to a multi-component mix of some or all these?

In a previous study we have shown that treating acutely sick and frail older patients in a care pathway based on a geriatric evaluation and management service significantly reduced mortality and also improved patients' chances of living at home [20,21]. Therefore, it would seem reasonable that frail old hip fracture patients would benefit from comprehensive geriatric assessment (CGA) in the acute setting. Evaluation of efficiency of care pathways for hip fracture patients should emphasise both survival, general function; especially mobility and physical activity, but also quality of life (QoL) and caregiver burden, as well as costs. There is a strong focus in health care management today on the efficient use of limited resources, especially on shortening of length of stay (LOS) and lowering of costs. Furthermore, over the years LOS for patients with hip fracture has declined irrespective of settings and the organizing of health care, indicating that new models of care are less costly than traditional clinical pathways. However, shortening of LOS and reduced emphasis on acute and in-hospital rehabilitation may increase admission rates to nursing homes and reduce the quantity and quality of rehabilitation, and consequently reduce recovery of walking ability and function [22,23] and also shift costs between sectors.

In the present study we aim to investigate whether an alternative clinical pathway for hip fracture patients during the in-hospital acute phase applying CGA in an orthogeriatric ward may improve outcomes in the short (1 and 4 months postoperatively) and long (12 months postoperatively) term without introducing additional specific follow-up programs. Hopefully we will increase the knowledge of whether in-hospital treatment of hip fracture patients in a geriatric acute-unit primarily will improve mobility, and secondly increase the chance of being discharged to and live in their own homes, and improve function and self-rated health, while maintaining the new care pathway cost-neutral in comparison to treatment in a traditional orthopaedic unit.

In accordance with general guidelines for the development, evaluation and reporting of randomized controlled trials (RCT) for complex interventions [24] the purpose of the this paper is to present context and study design, a short description of intervention, outcome measures and power calculations and also procedures for the Trondheim Hip Fracture Trial. An extensive report on the intervention program will be published later.

### Aims

#### Primary aim

• To estimate the effect on mobility 4 months after surgery of treating hip fracture patients in an orthogeriatric ward as compared to treatment in an orthopaedic ward.

#### Secondary aims

• To estimate the effect of the intervention on place of residence, gait, activities of daily living, mood and health related quality of life 1, 4 and 12 months postoperatively.

• To investigate change in gait control and daily physical activity through one year after surgery.

• To estimate the effect of the intervention on the use of health care resources and survival.

• To estimate the effect of the intervention on fear of falling and falls 4 and 12 months postoperatively.

## Methods/design

### Project context

The present study is conducted at St. Olav Hospital, the University Hospital of Trondheim, Mid-Norway. St. Olav Hospital also serves as a local hospital for 280.000 inhabitants of Soer-Troendelag County, admitting all hip fracture patients from this catchment area.

During the study period the Department of Orthopaedics will run a Trauma Unit consisting of 19 beds for inpatient orthopaedic care. While in the Emergency Department hip fracture patients are examined by the orthopaedic resident on call who in collaboration with the orthopaedic surgeon in charge establishes diagnoses and indication for surgery.

The Department of Geriatrics is organised as a formal unit of the Clinic of Internal Medicine consisting of a 10 bed-ward of acute geriatrics services linked to an out-patient facility. During a recent hospital reorganisation with cutting down of beds in the Department of Orthopaedics an orthogeriatric 5 bed-unit was established as an additional but still integrated part of the acute geriatric ward.

Being a new service for hip fracture patients routinely offered in parallel with the traditional orthopaedic care pathway, it was decided to evaluate potential benefits of this unit, now investigated through the present study. Enrolment of study patients was planned to start after a 4 months clinical run-in period for the new unit.

### Study design

The study is designed as a RCT with parallel groups where the intervention of interest, a CGA and management of hip fracture patients taking place in this orthogeriatric unit is compared with traditional care in an orthopaedic ward.

### Study population

All people over 70 years of age, with an acute hip fracture, previously being able to walk 10 meters, and living in their own homes or staying temporarily in an institution, suffering an intracapsular, trochanteric or subtrochanteric fracture, and able to give an informed consent, are invited.

Excluded are patients with pathological fractures or multi trauma injuries or with terminal illness not expected to live longer than 3 months or patients who have already been enrolled in this study. At study start the catchment area consisted of the City of Trondheim and the nearest municipalities. In case of slow recruitment we will use the option of expanding the catchment area to comprise all municipalities of Soer-Troendelag.

### Intervention

Patients randomised to the intervention group are transferred directly from the Emergency Department to the orthogeriatric ward while control patients are transferred to the trauma unit at Department of Orthopaedic Surgery. Orthopaedic surgeons are responsible for the initial assessment, diagnosing of the fracture and decisions on type of surgery for both groups. Anaesthesiologists make preoperative assessments regarding analgesia, operability and perioperative anaesthesiological procedures. After surgery and for a limited time period all patients are observed in the recovery unit.

On request orthopaedic surgeons examine study patients in the orthogeriatric ward and supervise the staff. Geriatricians serve the orthopaedic ward equivalently.

The experimental intervention program is offered only during the acute hospital stay. The orthopaedic surgeons decide on traditional follow-up consultations after discharge irrespective of group allocation.

#### Experimental group

Physicians at the Department of Geriatrics or residents on call have the 24-hour medical responsibility pre- and postoperatively.

The treatment strategy is based upon CGA which is a systematic and multidimensional diagnostic process focusing on evaluation of frail elderly persons' medical, psychosocial and functional capabilities and limitations in order to develop a coordinated and integrated plan for treatment and long-term follow-up by the primary health care system [25]. An interdisciplinary team consisting of geriatricians and residents, nurses, physiotherapists and occupational therapists with special competence in geriatrics is responsible for the CGA program. The team emphasizes adequate nutrition, early mobilization and functioning in activities of daily living, initial in-hospital rehabilitation and early discharge planning. Discharge planning starts as early as possible involving all team members. Whenever possible, patients are recommended to receive post discharge rehabilitation in their own home. In addition to treatment of current medical conditions, the management program also focuses on factors related to the fall incident causing the fracture.

#### Control group

Control patients receive traditional treatment at the Trauma Unit and follow-up at the Orthopaedic Out-patient Clinic. All patients are referred for in-hospital physiotherapy. Staff nurses are responsible for the discharge planning.

### Measures

***Mobility*** as primary outcome is assessed using the composite measure of the Short Physical Performance Battery (SPPB) [26,27]. SPPB consists of three tasks: 10 second of standing balance in three different positions (side-by-side, semi-tandem and tandem); 4 meter timed walking at preferred speed; and time to rise from a chair five times [26]. Each task is scored on a 0-4 scale. A score of 0 is given if the participant is unable to complete the task. Scoring from 1-4 for each task is assigned based on quartiles of performance derived from the Established Populations for the Epidemiologic Study of the Elderly (EPESE) [27]. A summary score ranging from 0-12, with 12 as the best score is created by summation of scores from the three tasks. The test is suitable for scoring persons with a large range of functional levels. It has been shown to have acceptable internal consistency (Chronbach alpha = 0.76) and test-retest reliability [28], ability to predict functional decline, rehospitalisation and death in older patients after hospitalization [29] and also to measure change in mobility in hip fracture patients.

***Mobility ***as secondary outcome is measured by the Timed Up & Go (TUG). According to the procedure time needed to rise from a chair, walk 3 meters, turn and walk back and sit down is measured [30]. The test is performed twice and the mean time (seconds) of the two trials is used as outcome. In the original paper by Podsiadlo the second of two trials is used, while in an earlier intervention study we have described high reliability of using the mean of two [31]. For participants not able to complete two trials, only one trial is used. Participants are instructed to use walking aids support if used regularly. Repeated tests aim to obtain fast speed while preserving safety, irrespective of using walking aids or not. TUG is well validated [30] and has been used in several studies on hip-fracture patients to predict falls [32], to assess functional mobility [33-35] and to assess effect of home-based therapy [36]. A limitation of using TUG is that scoring presupposes that the person is able to perform all sub-components of the task. Mobility and mobilisation during the index stay will be measures by use of Cumulated Ambulation Score (CAS) [37].

***Place of residence*** is used as a secondary outcome. Registrations of place of residence and change in place of residence are based on Gerica - the Electronic Health Record (EHR) of municipality of Trondheim by a procedure similar to one we have reported previously [20]. The typology differentiates between patients living in their own home, sheltered housing, nursing home, rehabilitation facility or hospital, respectively.

***Activities of daily living (ADL) ***is measured using the Barthel Index [38] and Nottingham extended I-ADL scale [39] based on reports, if possible from the patient, from next of kin or from nursing staff. Supplementing Gerica ADL-scores are filled in by community nursing staff. The Barthel Index evaluates a patient's self-care abilities in 10 areas, including bowel and bladder control. The scoring depends on the person's need for help such as in feeding, bathing, dressing, and walking. The Barthel index was constructed for stroke patients but has also been extensively used in hip fracture patients. I-ADL scales measure a series of life functions necessary for maintaining a person's immediate environment-eg, obtaining food, cooking, laundering, house cleaning and phone use. The Nottingham extended I-ADL scale has been shown to be reliable and valid in patients undergoing surgery for osteoarthritis but may underestimate the sizes of the health gain, at least after arthoplasty [40].

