#### Gait

Gait assessments are recorded for a subset of participants being able to walk without assistance from another person and attending the 4- and/or 12-month evaluations at the outpatient clinic. These measurements are performed using an electronic gait mat GaitRite^® ^which is regarded a reliable measure of spatio-temporal gait parameters also in elderly and frail people [44-46]. Participants should preferably walk the gait mat without walking aids. ***Physical activity ***is monitored in all patients when sensors are available for use. For these measurements we are using the small body worn accelerometer-based sensor ActivPal^®^[47], which is undergoing extensive evaluation in our research group [48].

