	NRS-pain	NRS-pain
ActivPal (24 hours)		ActivPal (4 days)
		GaitRite
Hand grip strength	Hand grip strength	Hand grip strength
		Quadriceps strength
Before fracture:		
Barthel Index	Barthel Index	Barthel Index
NEIADL	NEIADL	NEIADL
Falls	Falls	Falls
Walking aids	Walking aids	Walking aids
CDR	CDR	CDR

Abbreviations: CAS = Cumulative Ambulation score, CDR = Clinical Dementia Rating, EQ-5D = EuroQual-5 Domains, FES-I = Falls Efficacy Scale-International, GDS-15 = Geriatric Depression Scale, MMSE = Mini Mental State Examination, NEIADL = Nottingham extended Instrumental Activities of Daily Living, NRS = Numeric Rating Scale, SPPB = Short Physical Performance Battery, TUG = Timed Up & Go.

The 4-month registration is performed by a research assistant at the hospital out-patient facility applying the present infrastructure for testing aspects of mobility and gait using the electronic gait mat. To secure maximal study compliance and low attrition rate, transportation both to and fro is taken care of by the same experienced taxi driver. An ActivPal sensor is worn for at least a 96-hour period of activity monitoring. Participants are urged to be tested at the hospital. In case of extensively impaired physical or mental capacity a pragmatic and reduced test protocol is applied in their own home or where they are staying for the time being. The time window is 4 months ± 2 weeks. For details on data collection and questionnaires, see Table 1.

The 12-month registration is performed similar to the 4-month registration. The time window is 12 months ± 4 weeks. For details on data collection and questionnaires, see Table 1.

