### Power and statistical analyses

Sample size estimates are based on mobility assessed by SPPB at 4 months following the fracture. A change in the SPPB score of 0.5 points is considered a small but meaningful change, while 1 point is considered a more substantial change. In order to detect an effect size of 1.0 when power is 80% and alpha = 0.05, a sample size of 304 participants would be needed. Based on data from a previous prospective observational study in a similar study population (work in progress), we expect a drop out rate of 10% due to death and 10% due to withdrawals during the first 4 months following the fracture. To allow for 304 patients to remain in the project at four months after the fracture 380 persons need to be included. Thus, the plan is to include a total sample of 400 participants. The assumptions underlying the sample size (i.e. the standard deviation at baseline) has been checked by an independent clinical trials unit after the first 200 patients enrolled, and found to be acceptable.

All data will be analysed and presented according to the updated CONSORT guidelines for reporting parallel group trials[60]. Patterns of missing data will be explored prior to analysis, and accounted for in the analysis by imputation methods [61]. To study differences in change between groups we will use multivariate analyses by use of mixed models for longitudinal data by general linear modelling (GLM) for continuous outcomes and by logistic regression for binary outcomes [62]. To study associations between the new clinical pathway and time to events, we will use Kaplan Meyer plots and the Cox proportional hazards regression model. In all analyses we will control for confounding factors and interactions and present both unadjusted and adjusted effects with 95% confidence intervals.

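### TUG and gait-mat outcomes have no value for patients who cannot perform them, so the stated analyses can shrink, and in some conditions reverse, a true benefit on these secondary outcomes

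*Protocol article*

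**What the plan says.** All references are to the protocol article.

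- **TUG (Measures).** TUG is the secondary mobility outcome: "The test is performed twice and the mean time (seconds) of the two trials is used as outcome". The rule for incomplete tests covers one completed trial: "For participants not able to complete two trials, only one trial is used". None is given for zero completed trials, although the same paragraph states the limitation: "A limitation of using TUG is that scoring presupposes that the person is able to perform all sub-components of the task".
- **SPPB (Measures).** For the primary outcome the matter is settled: "A score of 0 is given if the participant is unable to complete the task".
- **Gait mat (Gait).** "Gait assessments are recorded for a subset of participants being able to walk without assistance from another person". The same sentence also requires attendance at the 4- and/or 12-month clinic visit. Under Data collection, the most impaired are tested elsewhere: "In case of extensively impaired physical or mental capacity a pragmatic and reduced test protocol is applied in their own home".
- **Aim (Secondary aims).** "To estimate the effect of the intervention on place of residence, gait, activities of daily living, mood and health related quality of life", at 1, 4 and 12 months.
- **Analysis (Power and statistical analyses).** Continuous outcomes go to mixed models for longitudinal data. On missing data: "Patterns of missing data will be explored prior to analysis, and accounted for in the analysis by imputation methods". Inability, death and withdrawal are not separated.

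**The concern.** Whether a patient can do the TUG, or walk unaided across a gait mat at the clinic, is known only after randomisation and is plausibly affected by treatment. Every participant could walk 10 metres before the fracture, so inability at follow-up is largely a consequence of the fracture and the care that followed. The intervention emphasises early mobilisation and function.

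Suppose the orthogeriatric unit gets more frail patients back on their feet. They then enter the intervention arm's mean with slow times, while their counterparts in the control arm contribute nothing. The two sets of performers are no longer comparable as randomised.

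Imputation does not repair this. It targets all patients, but it gives those who cannot do the test a hypothetical time extrapolated from those who can.

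At stake is a secondary mobility result that understates a real gain or, in some circumstances, points the opposite way to SPPB and is read as evidence against the intervention.

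**Working it through.** **The plan's own figures.** The article gives no figure for TUG or gait, so there is none to reproduce. Its one computed figure concerns SPPB: 304 / (1 − 0.20) = 380, which agrees. Nothing below touches it.

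**Step 1: exact arithmetic on the performers' mean.** Assumed inputs, none from the article: a share a = 0.70 of controls can do TUG, with mean m = 25 s. Treatment speeds these patients by g seconds and makes a further share q able, at S = 45 s. Then

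treated minus control = [a(m − g) + qS]/(a + q) − m = [q(S − m) − ag]/(a + q).

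A positive value makes treatment look worse.

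| g (s) | q = 0.05 | q = 0.10 |
|---|---|---|
| 0 | +1.33 s | +2.50 s |
| 1 | (1.00 − 0.70)/0.75 = +0.40 s | (2.00 − 0.70)/0.80 = +1.62 s |
| 2 | (1.00 − 1.40)/0.75 = −0.53 s | (2.00 − 1.40)/0.80 = +0.75 s |
| 3 | (1.00 − 2.10)/0.75 = −1.47 s | (2.00 − 2.10)/0.80 = −0.12 s |

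In every cell no patient is harmed and some gain. The sign turns when q exceeds ag/(S − m) = 0.70g/20, which is 3.5% for a 1 s gain and 7% for a 2 s gain. With m = 22 s and g = 0 the differences are 0.05 × 23/0.75 = +1.53 s and 0.10 × 23/0.80 = +2.88 s.

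**Step 2: does the shape of the benefit matter?** Assumed model: mobility is a standard normal score and TUG is log-normal (median 25 s, log-SD 0.45). Patients beyond a threshold are unable, set so that 20, 30 or 40% of controls are unable. The true effect in everyone includes hypothetical times for the unable, so it exists only within the model.

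| Benefit | Controls unable | True, everyone | True, able under either arm | Performers only |
|---|---|---|---|---|
| Uniform, 0.32 SD | 20% | −3.71 s | −3.03 s | −1.77 s |
| | 30% | −3.71 s | −2.81 s | −1.39 s |
| | 40% | −3.71 s | −2.61 s | −1.11 s |
| Worst 40% only, 0.6 SD | 20% | −3.78 s | −1.89 s | −0.43 s |
| | 30% | −3.79 s | −1.01 s | +0.46 s |
| | 40% | −3.78 s | 0.00 s | +1.24 s |

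With a uniform benefit, the performers-only estimate is smaller than the effect in always-able patients by 1 − 1.77/3.03 = 42%, 1 − 1.39/2.81 = 51% and 1 − 1.11/2.61 = 57%. The sign stays right. With benefit confined to the worst 40%, the sign is wrong at 30% unable and above.

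**Step 3: does imputation help, and does ranking?** I simulated 2000 trials of 160 per arm (400 × 0.8 / 2). Missing times were imputed by regression on arm and one pre-fracture covariate (correlation 0.6 with mobility), with random residuals. For the benefit confined to the worst 40%:

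| Controls unable | Performers only, wrong sign | Imputed: mean difference | Imputed: wrong sign | Inability ranked worst, wrong direction |
|---|---|---|---|---|
| 20% | 29% | −0.86 s | 15% | 1% |
| 30% | 73% | +0.01 s | 50% | 1% |
| 40% | 97% | +0.80 s | 85% | 2% |

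Imputation lessens the bias without removing it. Across both benefit shapes, ranking inability as worst gave the wrong direction in at most 2% of trials, with power of 0.53 to 0.79.

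**The case against.** **Much of this could sit in an analysis plan.** A rule for zero completed TUG trials is the kind of detail such a plan often holds, and neither that plan nor the full protocol is shown. The bare absence of a rule would therefore be no finding. What remains is what the article itself fixes: TUG in seconds, a gait sample selected after randomisation, gait as an effect to be estimated, and a general imputation rule. Followed as written, these give a biased comparison.

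**The limitation is disclosed.** The article admits the TUG problem, calls the gait sample a subset, and has SPPB at every visit with inability scored 0. That protects the primary conclusion and gives a reader something to set beside TUG. Disclosure does not say how the unable are analysed.

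**Stronger readings that the document does not support:**

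- *That the plan will reverse a true benefit.* Reversal needs benefit concentrated near the threshold of ability. A uniform benefit is only attenuated, and even the concentrated benefit kept the right expected sign at 20% unable. All inputs are assumed. The 43% in the Background who lost outdoor mobility is not a proportion unable to do TUG.
- *That the article commits to imputing a TUG time for someone who cannot stand.* It names neither TUG nor the gait mat in its imputation sentence. The wording permits this without stating it.
- *That imputation estimates an effect in a selected group.* It estimates a hypothetical quantity in everyone.
- *That the aim's 1-month gait assessment contradicts Table 1, which has GaitRite only at 4 and 12 months.* The aim does not define gait as gait-mat parameters, and SPPB at 1 month includes a timed 4-metre walk. The two can be read together.

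**Conclusion.** The point stands as a weakness in secondary outcomes that should be corrected. The selection follows from the article's own definitions and needs no assumption. Its effect on the result does: attenuation under a uniform benefit, and possible reversal if the gain lies mainly in patients near the threshold of ability. The figures above show what is possible and do not predict this trial, because the article gives no TUG mean, spread or proportion unable. The primary SPPB analysis scores inability as 0 and is not affected in this way. The sample size is untouched.

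**What to change.** **TUG.** Treat inability as an outcome, as SPPB already does. Give it the worst rank, or analyse speed (6 m divided by time, the test being 3 m out and back) with inability set to 0, using a rank-based or ordinal comparison. Report the proportion able by arm. Restrict imputation to values missing for reasons other than inability or death, which requires the reason for each missing test to be recorded. Mean seconds among completers can still be shown, labelled descriptive.

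**GaitRite.** Report by arm the proportion able to walk unassisted and attending the clinic. Label comparisons of gait parameters as descriptive among independent walkers at 4 and 12 months.

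**What the fix leaves open.** The TUG analysis would still condition on being alive and assessed, and the article expects 10% deaths and 10% withdrawals by 4 months. State this, and report deaths by arm beside the result.

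**Cost.** A change of wording in the analysis plan. No new test is needed, and the article places itself before the start of data analysis, so the rule could still be set in advance. The drawback is that a rank or speed result is less familiar to clinicians than mean seconds.
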